## Abstract

**Background:**

About 9 % of all children in Germany are born preterm. Despite significant improvements of medical care, preterm infants are at a greater risk to develop short and long term health complications. Negative consequences of preterm birth include neurodevelopmental disabilities, behavioral problems or learning disorders. Most data on effects of prematurity are derived from single or multi-center studies and not population-based.

Since some of the long term problems of preterm delivery are associated with a disturbed parent-child interaction originating in the neonatal period, several intervention programs became available aiming to strengthen the early parent-child relationship. However, there is insufficient knowledge regarding the psychosocial and socioeconomic impact of these interventions. Prior to introducing them into routine care, those effects have to be rigorously evaluated.

The population-based cohort study EcoCare-PIn (Early comprehensive Care of Preterm Infants—effects on quality of life, childhood development, and healthcare utilization) will investigate the following primary research questions: 1) What are the short- and long-term consequences of preterm birth with regard to parental stress, parent-child relationship, childhood development, quality of life and healthcare utilization including costs?

2) Does early family-centered psychosocial care prevent the hypothesized negative consequences of preterm birth on the above mentioned outcomes?

**Methods/Design:**

EcoCare-PIn examines the research questions by means of a linkage of a) pseudonymized administrative individual-level claims data from the German statutory health insurance AOK PLUS on approximately 140,000 children born between 2007 and 2013 in Saxony, and b) primary data collected from the parents/caregivers of all very low birth weight (<1,500 g; *n* = 1,000) and low birth weight infants (1,500 to 2,500 g; *n* = 5,500) and a matched sample of infants above 2,500 g birth weight (*n* = 10,000).

**Discussion:**

In Saxony, approximately 50 % of all individuals are insured at the AOK PLUS. The linkage of patient-level administrative and primary data is a novel approach in neonatal research and probably the only way to overcome shortcomings of studies solely relying on one data source. The study results are based on an observation period of up to 8 years and will directly inform perinatal healthcare provision in Saxony and Germany as a whole.

## Background

About 9 % of all infants are born prematurely, i.e. prior to completing 37 weeks of gestation [1, 2]. Advances in perinatal care during the last decades resulted in a significantly decreased mortality of preterm infants and a reduction of severe organ damage [3, 4]. Nevertheless, preterm born children are still at a higher risk of long-term health and developmental problems compared to their term born counterparts. Known consequences of preterm birth include but are not limited to motor or sensory impairments, learning disabilities or behavioral problems [5–12]. These disturbances bear the potential to compromise the quality of life of affected children and families [13, 14], but also constitute a substantial burden for the healthcare system [15–17]. Whereas impairment can be explained to some extent by organ damage, great variations in development are found despite a similar pattern of injury [18].

Socioeconomic parameters and the quality of the parent-child-relationship have been identified as important determinants of the long-term development of children [19–21]. Especially the parent-child-relationship is significantly affected by preterm delivery, since the immaturity of the newborn interferes with the physiological process of postnatal bonding and attachment. Starting before birth, the complex process of attachment is an essential part of the parental behavioral system that prepares adults for caregiving [22]. It can be disturbed by the premature interruption of pregnancy, an early separation of the newborn from the parents due to necessary medical treatments and the immature babies’ limited attachment behaviors during the first months of life (e.g. smiling, babbling). These circumstances make it more difficult for parents to affectively interact with their child [23, 24] and therefore represent a significant barrier to the development of a well-functioning parent-child relationship early in life [25].

High levels of parental stress, which have frequently been reported when children are born preterm [26–28], are another risk factor for a healthy child development [29].

Existing evidence on the consequences of preterm birth is strongly based on single or multicenter studies that investigated a small selection of outcomes and/or are focused on special groups of preterm infants. For a more comprehensive picture, there is a need for large-scale population-based studies that include all infants regardless of gestational age and investigate the consequences of preterm birth over a substantial time period for affected children, families and the healthcare system. Studies that link individual-level questionnaire data and administrative health insurance data offer great opportunities for the investigation of the broad spectrum of clinical, psychosocial and socioeconomic outcomes of preterm birth, but are still novel in the field.

### Family-centered care program (FamilieNetz)

Following the increased knowledge about the adverse consequences of preterm birth on child and family, but also on the healthcare system, different psychosocial interventions for parents of preterm infants have been developed with the aim to improve the early parent-child-relationship and reduce parental stress [30–35]. However, existing interventions in Germany are not standardized and have not been evaluated rigorously, making it difficult to draw firm conclusions on their preventive effects [36–38].

A novel support and training program for families of sick newborns and preterm infants (FamilieNetz) was developed and introduced in clinical routine at the Department of Neonatology and Pediatric Intensive Care at the University Hospital Carl Gustav Carus, Dresden in 2009. The comprehensive program consists of different interventions, including parent counseling, parent education and discharge planning. Its philosophy focuses on empowering parents in primary caregiving for their child and involving them in daily routine as early as possible by giving them psychological and social-medical support during the initial hospital stay [39].

Single components of the intervention program have been evaluated and as a consequence health insurance companies in Saxony are compensating it in part since 2012. In a next step, the program shall be introduced into other perinatal centers in Saxony and later in Germany as well. However, prior to the introduction, a comprehensive evaluation of the whole multiple component approach is required, in accordance with the principles of evidence-based healthcare.

In order to address the issues outlined above, the study EcoCare-PIn will examine the following research questions:What are the short- and long-term consequences of preterm birth with regard to parental stress, parent-child relationship, family and child quality of life, child development, and healthcare utilization including costs?Does early family-centered psychosocial care prevent the hypothesized negative consequences of preterm birth on parental stress, parent-child relationship, family and child quality of life, child development, and healthcare utilization including costs?

#### Hypotheses

Preterm birth and subsequent need for medical treatment disturbs the process of postnatal attachment and will have an impact on (I) parental stress, parent-child-relationship, and quality of life of family and child at age 1–7 years (primary outcomes) and (II) mental and physical child development (e.g. school performance, comorbidities), healthcare utilization and cost (secondary outcomes) during that time of life.Early psychosocial intervention that aims to support attachment and parental competency improves the parent-child-relationship and modifies the hypothesized adverse short and long-term consequences of preterm birth for the child, the child’s family, and the healthcare system.

The hypothesized causal model is shown in Fig. 1.

**Fig. 1 Fig1:**
[figure not shown]
Hypothesized causal model (adapted from: Reichert & Rüdiger, 2012 [39])

## Methods/Design

EcoCare-PIn is a cohort study comprising the linkage of individual-level data from two different sources: (1) administrative claims data from the German statutory health insurance AOK PLUS on all insured children born between 2007 and 2013 in Saxony and (2) primary data collected by means of questionnaires (in 2014/2015) from parents or legal caregivers of VLBW (very low birth weight) infants (<1,500 g), LBW (low birth weight) infants (1,500 to 2,499 g), and infants with a birth weight of 2,500 g or higher as controls.

Preterm birth is generally defined as birth before 37 completed weeks of gestation [2]. As there is considerable overlap between gestational age under 37 weeks and birth weight below 2,500 g, the use of birth weight (<2,500 g) for the definition of preterm born children instead of gestational age (<37 weeks) can be regarded as an acceptable approach in case that data on gestational age are not available or of uncertain quality [40, 41]. As the AOK PLUS does not provide data on gestational age, but on birth weight, we will use the latter as proxy measure for preterm birth.

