### Design and recruitment

The study is based on pseudonymized *administrative outpatient and inpatient data* of all children born in Saxony between January 1^st^, 2007 and December 31^st^, 2013 with health insurance at the AOK PLUS. The whole cohort of newborns will include almost 140,000 children, with approximately 1,000 VLBW- and 5,500 LBW-children among them. A broad set of insurance data will be provided and analyzed within this study, including birth weight (classified into <1,500 g (VLBW), 1,500–2,499 g (LBW) and ≥2,500 g (controls)), selected sociodemographic characteristics of children (age, sex, first three digits of ZIP code), diagnoses (ICD-10 codes), diagnosis related billing information (DRG-codes), prescriptions (PZN-codes, ATC-codes, cost), medical procedures (OPS-codes), claim codes for outpatient services and procedures (EBM-codes) and data of healthcare providers (discipline, first three digits of ZIP code) [42]. Based upon these pseudonymized administrative data, we will investigate and compare VLBW-, LBW- and control children with regard to mental and physical development, healthcare utilization and cost from birth through December 31^st^, 2013.

To enable further analyses, additional *primary data* will be collected on a subgroup of the described cohort of children. With support from the AOK PLUS, parents or legal caregivers from all preterm born children and parents/legal caregivers of a matched sample of 10,000 control children will be approached via postal questionnaires. Control children for the primary data collection will be selected via frequency matching according to birth year, sex and administrative district.

The questionnaire will cover information on parental stress, parent-child relationship, child’s physical and mental development (including school performance), quality of life of children, family quality of life, sociodemographic characteristics of parents, and exposure to psychosocial care in the neonatal period. These primary data will be linked to the administrative data on an individual level.

Figure 2 provides a flow chart on the design of the study.

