### Instruments

The following instruments will be used as part of the primary data collection to assess parental stress, parent-child-relationship, mental development and quality of life. These tests are widely used, valid, reliable, and available in German language:parental stress and parentchild relationshipEBI [Eltern-Belastungs-Inventar] (german version of PSI [Parenting stress index]); Tröster H 2011 [43].mental development of childrenSDQ [Strengths and Difficulties Questionnaire]; Goodman R 1997 [44].quality of lifeparents: WHOQOL-BREF [WHO-Quality of Life—brief version]; Angermeyer MC et al. 2000 [45].children: KINDL [Questionnaire for the collection of health-related quality of life in children and adolescents]; Ravens-Sieberer U, Bullinger M 1998 [46].

These instruments are incorporated into the study questionnaire after having obtained the respective author licenses. At the timepoint of submission of this study protocol, all necessary licenses had been obtained.

To meet the goal of assessing potential consequences of preterm birth not covered with these instruments (e.g. school performance, details on physical development) as well as details on psychosocial care in the neonatal period, the study questionnaire will also contain items developed by the authors and the scientific advisory board. The study questionnaire will be beta-tested and revised if necessary prior to application.

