### Data preparation

The classification into different birth weight groups (VLBW, LBW and controls) is based on documented birth weight and assigned directly by the health insurance company. In the absence of a documented birth weight, ‘unknown birth weight’ is encoded by the insurance. In order to limit the number of children in this group, those children will be reassigned by the authors according to the child`s inpatient or outpatient P07-ICD-diagnoses which directly refer to a specific birth weight (ICD-10-GM P07.0-, P07.00, P07.01, P07.02, P07.10 or P07.11^1^^a ^lead to reassignment to the VLBW-group; P07.1- or P07.12^b^ lead to reassignment to the LBW-group).

In case there is none of the mentioned birth weight specific diagnoses it will be checked whether a hospital admission within the first 7 days after birth has been coded and a documented admission weight is available. If both criteria are fulfilled, the child will be reassigned in accordance with the given admission weight to the VLBW, LBW or control group.

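### On the article's own figures, birth weight below 2,500 g leaves about half of preterm infants among the controls, so the results will describe low birth weight and not preterm birth

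*Protocol article*

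**What the plan says.** The research questions and hypotheses concern preterm birth. The Background gives its definition and frequency: "About 9 % of all infants are born prematurely, i.e. prior to completing 37 weeks of gestation". The abstract gives the same figure for Germany: "About 9 % of all children in Germany are born preterm".

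Methods/Design repeats the 37-week definition and describes the overlap with birth weight under 2,500 g as considerable, without a figure. It accepts birth weight as a substitute where gestational age is missing or its quality is doubtful. The insurer's data hold no gestational age, "but on birth weight, we will use the latter as proxy measure for preterm birth". Every child of 2,500 g or more is a control.

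Design and recruitment gives the expected counts: "The whole cohort of newborns will include almost 140,000 children, with approximately 1,000 VLBW- and 5,500 LBW-children among them". Questionnaires go to "parents or legal caregivers from all preterm born children" and to caregivers of 10,000 controls, frequency-matched on birth year, sex and district. The Statistical analysis section models birth weight class, adjusted for sex, birth year and socioeconomic status.

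Under Instruments, the questionnaire is to include items written by the study team, and it is still open to change: "The study questionnaire will be beta-tested and revised if necessary prior to application".

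**The concern.** A preterm rate of about 9 % and a low-birth-weight share of 4.6 % cannot describe nearly the same children. A large part of the preterm infants must weigh 2,500 g or more, and under the plan they are controls. Gestational age plays no part in the exposure, the matching or the adjustment described in the article.

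Two statements are affected. The overlap is weaker than the text suggests. The statement that caregivers of all preterm children are approached is also not true under the article's own 37-week definition, because heavier preterm children are reached only if they happen to be drawn as controls.

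What is at stake is the meaning of the main result. The contrast is low against normal birth weight. Read as an effect of preterm birth, it would be applied to a population of which about half was never in the exposed group. The Discussion says that the findings will inform health policy.

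**Working it through.** **Inputs from the article**
- Preterm rate: about 9 % (abstract and Background; a general or German rate, not one measured in this cohort).
- Cohort: about 140,000. Below 2,500 g: 1,000 + 5,500 = 6,500 (Design and recruitment).
- Controls approached: 10,000. Expected response: 30 % (Statistical analysis).

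The article gives no figure for the overlap, so there is none to reproduce.

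**Minimum share of preterm infants classed as controls**
- Share below 2,500 g: 6,500 / 140,000 = 4.6 %.
- Expected preterm: 0.09 × 140,000 = 12,600.
- Best case for the proxy, with every child below 2,500 g preterm: 12,600 − 6,500 = 6,100 classed as controls; 6,100 / 12,600 = 48.4 %.

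**Sensitivity to the preterm rate (assumed; all children below 2,500 g still taken as preterm)**

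| Preterm rate | Preterm | Classed as controls | Share |
|---|---|---|---|
| 7 % | 9,800 | 3,300 | 33.7 % |
| 8 % | 11,200 | 4,700 | 42.0 % |
| 9 % | 12,600 | 6,100 | 48.4 % |
| 10 % | 14,000 | 7,500 | 53.6 % |

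**Sensitivity to term infants below 2,500 g (assumed; rate 9 %)**
- 80 % of the 6,500 preterm: (12,600 − 5,200) / 12,600 = 58.7 %.
- 60 % preterm: (12,600 − 3,900) / 12,600 = 69.0 %.

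The article gives no figure for this share. Any value under 100 % makes the proxy look worse.

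**Effect on the control group**
- Controls in the cohort: 140,000 − 6,500 = 133,500.
- Preterm among them: 6,100 / 133,500 = 4.6 % (5.5 % and 6.5 % under the 80 % and 60 % assumptions).
- If heavier preterm children differ from term children by d on an outcome, the control mean shifts by about 0.046 × d.

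**Who is available in the linked data**
- Heavier preterm children among 10,000 sampled controls: 0.0457 × 10,000 ≈ 457; responders at 30 %: about 137.
- Responders below 2,500 g: 0.30 × 6,500 = 1,950.
- Heavier children among preterm responders: 137 / (137 + 1,950) = 6.6 %, against 48.4 % in the cohort.
- Sampling fraction at 2,500 g or more: 10,000 / 133,500 = 7.5 %, a weight of 13.35 against 1 for children below 2,500 g.
- Approximate effective number of preterm responders after weighting: (137 × 13.35 + 1,950)² / (137 × 13.35² + 1,950) ≈ 3,779² / 26,366 ≈ 542, out of 2,087.

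The last block takes the sampled controls to have the same preterm share as all controls, response to be equal across groups, and all children below 2,500 g to be preterm.

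**The case against.** The proxy is disclosed, with its reason and two cited sources, and the Statistical analysis section openly models birth weight. The article accepts the proxy not only where gestational age is missing but also where its quality is uncertain. Questionnaires sent in 2014/2015 about births from 2007 would rely on parental recall over up to about 8 years. The phrase about all preterm children can be read as the proxy-defined group. The 9 % is a rounded general rate, the counts are approximate, and some children have unknown birth weight. All of this stands. It makes the point one of interpretation and not of concealment, and it makes 48 % conditional. It does not close the gap between 9 % and 4.6 %, and the article does not argue that parents' reports would be too poor to use.

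Some stronger readings are tempting but unsupported:
- **The controls are heavily contaminated.** About half of preterm infants are misplaced, but they are under 5 % of controls in the base case, so the bias from this source is modest.
- **Weeks of gestation are not asked.** The questionnaire is not shown, and the item may already be there.
- **The missed children are the largest preterm group.** The article gives no distribution by week.
- **The claims file can identify them.** Data preparation names only "inpatient or outpatient P07-ICD-diagnoses which directly refer to a specific birth weight". Whether gestation-related codes are available is not shown.
- **A simple contrast of under 37 weeks against term would settle the matter.** Because sampling is by birth weight, an unweighted contrast would have about 7 % heavier children in its preterm group, where the cohort has about 48 %.

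**Conclusion.** The concern holds, as a mismatch between the question asked and the exposure analysed. If the general 9 % rate applies to this cohort, at least about 48 % of preterm infants are controls, and 34 to 42 % at assumed rates of 7 to 8 %. These minima take the article's approximate counts at face value and rest on the assumption most favourable to the proxy. The larger problem is the absence of heavier preterm infants from the exposed group. The primary outcomes come from the questionnaire, so the linked data are where a remedy is possible. The claims-only analysis can be put right mainly by its wording.

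**What to change.** 1. Make sure that the questionnaire asks completed weeks of gestation; if the item is absent, add it before mailing.
2. In the linked data, keep the birth-weight-class analysis, but remove children reported as preterm from the controls.
3. Add a prespecified analysis of under 37 weeks against term, weighted for the sampling design: all children below 2,500 g, about 7.5 % of those at or above it.
4. Report the observed overlap between weight class and reported gestation in place of the unquantified statement.
5. Correct the statement that caregivers of all preterm children are approached.
6. Word claims-only conclusions as effects of low birth weight. Use gestation-related diagnosis codes only if the claims file proves to hold them.

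The cost is at most one questionnaire item and one further analysis. Parental recall of weeks will carry error. Only about 137 heavier preterm responders are expected, and weighting them up by about 13 widens the intervals of the added analysis considerably, so it supplements the weight-class analysis and does not replace it. The control group loses about 137 of 3,000 expected responders.

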### Design and recruitment

The study is based on pseudonymized *administrative outpatient and inpatient data* of all children born in Saxony between January 1^st^, 2007 and December 31^st^, 2013 with health insurance at the AOK PLUS. The whole cohort of newborns will include almost 140,000 children, with approximately 1,000 VLBW- and 5,500 LBW-children among them. A broad set of insurance data will be provided and analyzed within this study, including birth weight (classified into <1,500 g (VLBW), 1,500–2,499 g (LBW) and ≥2,500 g (controls)), selected sociodemographic characteristics of children (age, sex, first three digits of ZIP code), diagnoses (ICD-10 codes), diagnosis related billing information (DRG-codes), prescriptions (PZN-codes, ATC-codes, cost), medical procedures (OPS-codes), claim codes for outpatient services and procedures (EBM-codes) and data of healthcare providers (discipline, first three digits of ZIP code) [42]. Based upon these pseudonymized administrative data, we will investigate and compare VLBW-, LBW- and control children with regard to mental and physical development, healthcare utilization and cost from birth through December 31^st^, 2013.

To enable further analyses, additional *primary data* will be collected on a subgroup of the described cohort of children. With support from the AOK PLUS, parents or legal caregivers from all preterm born children and parents/legal caregivers of a matched sample of 10,000 control children will be approached via postal questionnaires. Control children for the primary data collection will be selected via frequency matching according to birth year, sex and administrative district.

The questionnaire will cover information on parental stress, parent-child relationship, child’s physical and mental development (including school performance), quality of life of children, family quality of life, sociodemographic characteristics of parents, and exposure to psychosocial care in the neonatal period. These primary data will be linked to the administrative data on an individual level.

Figure 2 provides a flow chart on the design of the study.

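### The whole-cohort comparison of child development rests on claims data alone, so it cannot separate worse development from closer detection in children below 2,500 g

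*Protocol article*

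**What the plan says.** The Hypotheses section of the Protocol article lists child development as a secondary outcome, with school performance and comorbidities as examples. It places healthcare utilization and cost in the same list of outcomes expected to depend on preterm birth.

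Development is then measured from two sources.

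- **Claims, whole cohort** (Design and recruitment): the administrative data alone will be used to "compare VLBW-, LBW- and control children with regard to mental and physical development, healthcare utilization and cost from birth" to the end of 2013. The clinical content supplied is "diagnoses (ICD-10 codes), diagnosis related billing information (DRG-codes", plus prescriptions, procedures and outpatient claim codes. No developmental test result is among the listed fields.
- **Questionnaire, subgroup** (Methods/Design; Instruments): "primary data collected by means of questionnaires (in 2014/2015) from parents or legal caregivers". Mental development is measured by the SDQ. For physical development and school performance, "the study questionnaire will also contain items developed by the authors and the scientific advisory board".

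The Statistical analysis section adjusts the birth-weight comparison for sex, birth year and socioeconomic status. On claims quality it says only, in general terms, that it depends on documentation in care and on recording by the insurer. The Discussion calls the administrative data objective.

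**The concern.** A child with a developmental problem enters the claims outcome only if the child is seen and the problem is coded or treated. Children below 2,500 g may be seen more often, and the study's own hypothesis is that their use of care differs. The chance that a given impairment is recorded may then differ by exposure group. None of the three adjustment variables addresses this: birth year handles the unequal length of follow-up, not detection by birth weight.

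At stake is the interpretation of the largest analysis in the study. With about 140,000 children, a modest difference in detection can reach significance and be reported as a developmental consequence of preterm birth. The Discussion says the results will directly inform health policy.

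**Working it through.** **The plan's own figures.** The article gives no detection rate and no figure for this outcome, so there is nothing to reproduce on the point itself. The nearest figures are the detectable effects. For the linked dataset, 30 % of 16,500 is 4,950 children; a noncentral F test with three groups at 5 % and 80 % power gives f = 0.044, which agrees with the stated 0.045. For the whole cohort the same formula with 140,000 children gives 0.0083, not the stated 0.035. That is a separate matter, and nothing below uses either figure.

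**Inputs from the article.** VLBW 1,000; LBW 5,500; controls 140,000 − 6,500 = 133,500; response 30 %.

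**Assumed inputs.** True impairment 10 % in every birth-weight group; 60 % of impaired controls coded; 60–80 % of impaired children below 2,500 g coded; no unimpaired child coded.

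**Formulas.** Observed risk = true prevalence × coding probability. With equal prevalence the prevalence cancels, so the observed risk ratio is the ratio of coding probabilities. z = (p₁ − p₀) / √[p₁(1 − p₁)/n₁ + p₀(1 − p₀)/n₀], with p₀ = 0.10 × 0.60 = 0.06 and n₀ = 133,500.

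Example, LBW at 70 %: p₁ = 0.07; SE = √(0.0651/5,500 + 0.0564/133,500) = 0.0035; z = 0.01/0.0035 = 2.9.

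| Coded if impaired, below 2,500 g | Observed risk | Risk ratio | Odds ratio | z, LBW | z, VLBW |
|---|---|---|---|---|---|
| 60 % | 6.0 % | 1.00 | 1.00 | 0 | 0 |
| 65 % | 6.5 % | 1.08 | 1.09 | 1.5 | 0.6 |
| 70 % | 7.0 % | 1.17 | 1.18 | 2.9 | 1.2 |
| 80 % | 8.0 % | 1.33 | 1.36 | 5.4 | 2.3 |

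**Sensitivity to prevalence.** Pooling VLBW and LBW (6,500 against 133,500) and varying true prevalence from 5 % to 15 %, the probability of a significant excess with no true effect is 22–54 % at 65 % coding, 62–98 % at 70 %, and 99–100 % at 80 %.

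**Can the linked data show the gap?** Expected respondents: VLBW 0.30 × 1,000 = 300; below 2,500 g 0.30 × 6,500 = 1,950; controls 0.30 × 10,000 = 3,000. At 10 % impairment these contain about 30, 195 and 300 abnormal children.

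- VLBW alone: a coding probability of 70 % has a 95 % half-width of 1.96 × √(0.70 × 0.30/30) = 0.16.
- Pooled below 2,500 g against controls, 70 % v 60 %: half-width of the difference 1.96 × √(0.21/195 + 0.24/300) = 0.085.

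A 10-point gap is therefore beyond reach for VLBW alone and only just visible when the two groups are pooled.

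**The case against.** The strongest reply is that two sources are the design. The article justifies linkage as the way past the limits of a single source and describes the two as complementary. Comorbidities fit coded data, and school performance fits a questionnaire. This stands. A reader might infer that one endpoint has been given two contradictory definitions, but the text does not support that: it describes a broad domain measured in two ways.

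A second reply is that a condensed article properly leaves code lists, the choice of leading source and bias analyses to the full plan. This also stands, and their absence is not the point. What the article does state is that development will be compared across birth-weight groups from administrative data. A later code list could not remove the dependence on contact, because procedures, prescriptions and billing items need contact just as diagnoses do.

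Third, the detection rates are assumed. They are. The documents support neither their size nor their direction, and for VLBW two of the three gaps considered fall short of significance.

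Fourth, the questionnaire is no reference standard. Response is expected to be 30 %, the caregiver reports, and parental stress is itself hypothesized to depend on preterm birth. A reader might infer that the questionnaire would return a ratio of 1 where claims do not. That would need equal reporting accuracy and no selective response, and the documents establish neither.

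**Conclusion.** The concern holds as a limit on interpretation. As specified, the whole-cohort claims comparison measures diagnosed or treated problems, and a birth-weight difference in it cannot be attributed to development alone. Under the stated assumptions the spurious risk ratio is about 1.08–1.33. For LBW, z is 1.5 at 65 % coding and 2.9–5.4 at 70–80 %; for VLBW it is 0.6 and 1.2–2.3. With equal detection the bias is nil.

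It would go too far to infer that the claims result will be spurious or that significance is assured. The documents show the mechanism, not its size, and a true developmental difference may be present as well. The outcome is secondary. The primary outcomes (parental stress, parent-child relationship, quality of life) come from the questionnaire and are untouched.

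**What to change.** 1. Label and interpret the whole-cohort claims outcome as diagnosed or treated developmental disorder or comorbidity. Report it beside the questionnaire development result, treating neither as a gold standard.
2. In the linked dataset (about 4,950 children), report as a sensitivity analysis the proportion with a claims code among children with abnormal questionnaire results. Compare children below 2,500 g (VLBW and LBW pooled, about 1,950 respondents) with controls.
3. State the caveats of that check: selective response, parent report, and claims that end before the questionnaire is completed.
4. Show the whole-cohort ratios over a range of detection ratios, for example by dividing the observed risk ratio by 1.00, 1.08, 1.17 and 1.33. A single corrected estimate should not be given, because the linked data are too imprecise to support one.

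No new data are needed, since the linkage is already planned. The cost is some extra analysis and a narrower claim from the 140,000-child cohort.
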